## Abstract

**Background:**

Self-management of health refers to various actions and decisions that impact health outcomes. To improve health, independence, and quality of life (QoL) while reducing healthcare utilization and costs, patients’ self-management abilities can be enhanced. However, disease-specific self-management interventions may not be applicable for older adults with multiple illnesses. Instead, focusing on prevalent geriatric syndromes, such as frailty, cognitive decline, pain, incontinence, or impaired mobility, may be more beneficial. To achieve this, a detailed understanding of the specific needs of the older population is crucial.

**Methods:**

Patients who are 70 years old or older will be chosen from four geriatric hospitals, which include both inpatient and outpatient facilities. At baseline, each participant will undergo a comprehensive geriatric evaluation and answer various questionnaires that focus on their current self-management abilities, self-efficacy, anxiety, aging perception, and QoL. Moreover, extensive data on the presence and impact of geriatric syndromes will be gathered. Three and six months after the initial evaluation, follow-up assessments will be conducted to identify any changes in participants’ health, independence in daily activities, geriatric syndromes, cognition and mood, QoL, and self-management.

**Discussion:**

The present investigation aims to assess the factors that may facilitate or impede self-management in older adults afflicted with geriatric syndromes. Instead of concentrating on particular diseases, this study will analyze the association between self-management and geriatric syndromes. The information obtained will contribute to clinical expertise on the self-management habits of older adults and their effects on their well-being, autonomy, and overall QoL, as well as provide insights into geriatric syndromes. This valuable knowledge will be crucial for developing personalised programs to enhance self-management among older adults.

**Trial registration:**

German Trial Register (Deutsches Register Klinischer Studien) DRKS00031016.

## Background

The rise in chronic and age-related illnesses is directly linked to demographic change. This is especially true for older adults who suffer from multiple conditions simultaneously, leading to frequent hospital visits and increased healthcare costs [1, 2]. This puts a strain on healthcare systems and makes it difficult to provide adequate care [3–5]. In addition to individual illnesses such as diabetes, osteoporosis, or Parkinson’s disease, older age is often characterised by overarching geriatric syndromes (also called *geriatric* giants), such as frailty, instability, falls, incontinence, depression, and cognitive decline [6–8]. These syndromes are often more relevant to individuals than a single illness. This is particularly true in the face of multimorbidity, where it is difficult to assign symptoms to a single illness [3, 6, 9]. Despite the significance of geriatric syndromes, they are often overlooked in clinical practice due to a lack of complete understanding, necessitating further research to comprehend their impact [10]. However, various studies have confirmed a high prevalence of geriatric syndromes, which are associated with poor health outcomes and increased healthcare utilization [6–8]. For example, recent data from Möller and colleagues (2022) surveying more than 6700 older adults show higher rates of hospitalization, longer hospital stays, more frequent outpatient contact and higher levels of polypharmacy in patients with geriatric syndromes [8]. Using the same dataset, Liang et al. (2018) identified a prevalence rate for having at least one geriatric syndrome of approximately 65% among patients aged 65 to 74 years; this number rose to almost 80% among those aged 75 to 84 years [11]. As the population continues to age and the relevance of geriatric syndromes increases, it can be assumed that the frequent healthcare utilization due to geriatric syndromes may overload healthcare systems. Hence, self-management becomes critical to reducing the burden on healthcare systems and promoting independent participation in daily life [1, 8, 12–14]. Indeed, poor health outcomes, increased healthcare costs, and adverse health events are associated with ineffective utilization of self-management strategies at home [14, 15]. As Udlis [16] put it, “people cannot *not* self-manage”, as every choice made, whether regarding activity, diet, social interaction, or decision making, is a type of self-management. Thus, supporting patients in *how* they manage their health is crucial, as it is not a question of “*if*” they self-manage. As a result, the World Health Organization designated self-management improvement as a critical strategy for combating chronic illnesses [17].

The study of self-management has been a frequented area of research, with many clinical intervention trials being carried out [14, 18]. Despite this, there has been no agreement on definitions, measurements, or interventions related to self-management [16, 19]. This lack of consensus has led to many different definitions being used in research, making it difficult to compare studies and make systematic progress [18]. Aside from the variations in definitions, self-management is considered a complex and individualised behaviour that covers various health-related, social, and emotional factors and aims to improve disease management in the long term [20]. This behaviour incorporates daily tasks performed to control or mitigate the impact of illnesses on health, social life and well-being [21]. Overall, as Barlow and colleagues (2002) put it, self-management describes “the individual’s ability to manage the symptoms, treatment, physical and psychosocial consequences and life style changes” [22], taking into consideration symptom monitoring and appropriate behavioural and emotional responses [22].

Previous research has identified several important factors that influence self-management, including self-efficacy [23, 24], perceived control, and attitudes toward health [25], social support [23, 26], cognition [26], and physical and mental health [26]. For example, Banerjee and colleagues (2022) assessed self-management in patients with chronic back pain and identified physical disability/activity, depression, and catastrophizing thoughts as barriers to self-management [27]. An Iranian study on patients with diabetes furthermore highlights the positive impact of social support on self-management behaviour [23]. Previous interventions to improve self-management are often disease-specific [28–30] and therefore not appropriate for the older population due to multimorbidity. For example, if a patient has 5 different diagnoses, managing diabetes as one of them will not be able to eradicate the impact of Parkinson’s disease, osteoporosis, hypertension, and depression. As Allegrante and Wells (2019) say, “managing a specific disease condition as opposed to managing the patient,” [14] is not equipped to deal with multimorbidity, geriatric syndromes, and continuous age-related life changes. Aging is accompanied by continuous changes in health, independence, and social life, and older adults are particularly vulnerable, both physically and mentally. Attitudes towards aging, such as the perception of control over aging processes and belief in improvement, must also be considered when assessing self-management, as these have been shown to influence health behaviour [31–33]. Therefore, many previous studies have not adequately addressed the specific needs of older adults. To fully comprehend and improve overall health outcomes, it is essential to consider the complex interplay of multiple systems, instead of concentrating on disease-specific factors [18]. Consequently, several reviews emphasize the importance of conducting more comprehensive research on self-management and its associated factors to develop effective interventions [16, 19, 34].

To fully understand self-management in the older patient population, we devised an in-depth quantitative, multicenter, and longitudinal data collection that encompasses the characteristics of the older population and focuses on a multitude of factors involved in self-management. Through this process, we aim to achieve a comprehensive understanding of older patients` self-management abilities challenges, and opportunities. As most older adults suffer from multimorbidity, and thus targeting individual illnesses is not feasible, we plan to explore various geriatric syndromes and their impact on health as potential self-management targets. For this purpose, comprehensive data on geriatric syndromes must be collected.

## Methods/design

This study is part of a larger project aimed at improving self-management through an intervention trial. The manuscript outlines the procedure for collecting baseline and follow-up data, which will serve as the foundation for the intervention. The first objective of this data collection is to determine the prevalence and impact of geriatric syndromes in order to identify intervention targets that are relevant to the older population. The second objective is to understand the current self-management behaviour and abilities of older adults, including predictors, burdens, and barriers. This will help us understand the link between self-management and health outcomes, and identify the variables that need to be fostered to enable older adults to self-manage geriatric syndromes. The study procedure is described in detail below.

### Settings and participants

Adults aged ≥ 80 years (or ≥ 70 years with multimorbidity) will be recruited from the geriatric inpatient wards and outpatient settings of four German hospitals included in the Center for Geriatrics in Southern Saxony-Anhalt (Zentrum für Altersmedizin im südlichen Sachsen-Anhalt, ZASSA). Written informed consent will be obtained from all patients or their representatives, and the study will be conducted in accordance with the Declaration of Helsinki and the Good Scientific Practice. The local ethics committee of Halle University Hospital approved this study. To avoid selection bias, all patients admitted to the wards during the data collection period will be screened for eligibility. Patients will be excluded from the study if they decline to participate, have acute delirium or severe dementia, or are unable to perform any activities of daily living (ADLs) on their own (complete dependence, e.g. due to being bedridden) according to the Barthel Index [35]. The follow-up assessments will take place 3 and 6 months after a patient is discharged from hospital. Data collection is expected to be completed by June 2025.

The sample size calculation is based on the following considerations: for the exploratory analysis of predictors of self-management using linear regression, a minimum of 8 patients per covariate is necessary [36]. Thus, we planned 10 patients per covariate included in the model. When considering approximately 25 covariates (see below), a sample size of 250 is assumed to be sufficient for our analysis. For the longitudinal survey, we consider changes in ADL as an outcome parameter. For the exploratory analysis of ADL changes in the linear regression, 171 participants are necessary to detect a significant effect with a moderate effect according to Cohen (adjusted R^2^ = 0.13). When expecting a decline in ADL of at least 1 point by follow-up, a sample size of 204 subjects is required [37, 38]. Assuming a dropout rate of 30% due to the advanced age of our patients, the final desired sample size is 265 patients.

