### Statistical analyses

The multitude of variables included in the present data collection will allow for an encompassing exploratory and confirmatory analysis of the data. The main goal is to (a) identify the parameters that influence self-management, (b) assess how *self-management* influences future daily *functioning/independence*, and (c) estimate the association between *self-management* abilities and *QoL*. Therefore, as a first step, the *self-management* behaviours of older adults at baseline and their gradient until follow-up will be described. Regression with elastic net regularization [62] or (generalized) linear mixed models (LMMs/GLMMs) will be employed for cross-sectional and longitudinal data to understand how the included health-related, psychosocial, and environmental factors influence self-management as the outcome variable (ASAS-R) [49, 50].

Likewise, mixed models, structural equation (SEM) [63–65] and network analyses [63, 64] will be used to explore the association between *self-management* levels at baseline, and *independence* in ADLs and iADLS at baseline and follow-up. These analyses will furthermore be conducted to understand how baseline *self-management* and related variables influence the *QoL*.

Further exploratory analyses may address the influence of baseline self-management abilities on health outcomes at follow-up, the relative influence of *depressive symptoms* and *VoA* on self-management and health outcomes, and the interactive associations among predictors of self-management as assessed via network analysis or structural equation modelling (SEM).

Similarly, irrespective of self-management, the present data collection will provide a rich understanding of the prevalence and impact of geriatric syndromes in older adults and their impact on *self-management* and ADLs/iADLs.

All analyses will be conducted with a significance level of *p* = 0.05; 95% confidence intervals and effect sizes will be reported, wherever appropriate.

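### The 30% dropout allowance was added as 204 × 1.3 instead of 204 / 0.7, so 265 patients do not leave the 204 the plan requires

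*Protocol article*

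**What the plan says.** The second paragraph of Settings and participants in the protocol article gives three sample sizes and one enrolment target.

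- For the cross-sectional regression on predictors of self-management, at 10 patients per covariate and about 25 covariates, "a sample size of 250 is assumed to be sufficient for our analysis".
- For the regression of ADL changes, "171 participants are necessary to detect a significant effect with a moderate effect according to Cohen".
- For the decline itself, "When expecting a decline in ADL of at least 1 point by follow-up, a sample size of 204 subjects is required".

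The paragraph ends with the allowance for loss and the target: "Assuming a dropout rate of 30% due to the advanced age of our patients, the final desired sample size is 265 patients". It does not name the size to which the allowance was applied, or the formula. It gives no power, standard deviation or test for the 204.

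**The concern.** A dropout rate is a share of the patients enrolled. To keep n patients after a loss of 30%, n has to be divided by 0.70. Multiplying n by 1.30 adds 30% of the smaller number and always gives too few. The stated 265 looks like the product of that multiplication.

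The figure 265 is the only enrolment target in the article, and the finished study will be measured against it. If it was built this way, then under the plan's own dropout rate it misses the plan's own requirement for the decline in ADL by follow-up. That requirement bears on the primary longitudinal endpoint. Variables and data collection defines this endpoint as a composite of changes in ADLs and iADLs and defines what counts as a 1-point change in it.

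**Working it through.** **Inputs**, all from Settings and participants: required sizes 250, 171 and 204; dropout 30%; final size 265.

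**Step 1: reproduce the stated figure.** Each required size was inflated in both ways.

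| Required size | × 1.30 | / 0.70 |
|---|---|---|
| 171 | 222.3 | 244.3 |
| 204 | **265.2** | 291.4 |
| 250 | 325.0 | 357.1 |

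Only 204 × 1.30 gives 265.

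**Step 2: patients left at 30% dropout.** 265 × (1 − 0.30) = 185.5, so 185 or 186. The gap to 204 is 204 − 185.5 = 18.5 patients, and 18.5 / 204 = 9.1%.

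**Step 3: dropout that 265 can absorb.** (265 − 204) / 265 = 61 / 265 = 23.0%.

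**Step 4: chance of reaching 204 anyway.** If each of 265 patients stays independently with probability 0.70, the binomial probability of at least 204 completers is 0.7%.

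**Step 5: correct inflation.** 204 / (1 − 0.30) = 291.4, rounded up to 292. The shortfall in enrolment is 292 − 265 = 27.

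**Step 6: effect on power, under assumptions.** The plan states a 5% significance level but neither the power nor the test behind the 204. Assume a two-sided test at 5% whose signal grows with √n, and a design power of 80% or 90% at n = 204. Power at n = 185 is then Φ[(1.960 + z) × √(185/204) − 1.960], with √(185/204) = 0.952.

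- 80% design (z = 0.842): 2.802 × 0.952 − 1.960 = 0.71, so power is about 76%.
- 90% design (z = 1.282): 3.242 × 0.952 − 1.960 = 1.13, so power is about 87%.

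For a paired t-test under the same assumptions, the standardised change detectable with 80% power is 0.197 at n = 204 and 0.197 × √(204/185) = 0.207 at n = 185.

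**Step 7: the other two requirements.** The cross-sectional regression uses baseline data, and 265 exceeds 250. The ADL-change regression needs 171, and about 185 completers exceed that; enrolment for it would be 171 / 0.70 = 244.3, so 245. Only the 204 is missed.

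**The case against.** The strongest case on the other side concerns weight and scope rather than the arithmetic.

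- **The base is inferred.** The article does not say that 265 came from 204. This is true, but the 204 stands in the sentence just before the dropout allowance, and no other size gives 265 by either formula. The shortfall does not depend on the inference, since 265 × 0.70 is below 204 however 265 was reached.
- **The 204 may not be the size for the composite endpoint.** The text ties it to a 1-point decline in ADL, whereas the primary longitudinal endpoint also includes iADLs. The article does not settle this. The 1-point unit matches the definition given for the composite, so the link is reasonable, but it is not stated.
- **185 may understate the analysed sample.** Mixed models are among the planned analyses and can use patients seen at 3 but not at 6 months. Patients who cannot attend are telephoned, and the Barthel Index is part of that call. Some patients counted as lost may therefore contribute data. This does not rescue the allowance, because the 30% may already reflect telephone contact, and the plan itself sets 204 as the requirement and adds the allowance to protect it.
- **The consequence is small.** This stands. The study is observational, much of its analysis is exploratory, two of the three size requirements are still met, and the conditional loss of power is 3 to 4 percentage points. It limits the damage but does not make the printed figure right.

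**Conclusion.** The concern holds. The stated 265 is 204 increased by 30%, and under the plan's own dropout rate it leaves about 185 patients, 18 to 19 (9%) short of the 204 required. The correct enrolment is 292, which is 27 more. This rests only on the 204, 30% and 265 printed in the article. The fall in power, from 80% to about 76% or from 90% to about 87%, and the rise in the detectable standardised change from 0.197 to 0.207, rest on an assumed design power and a two-sided 5% test; the change in detectable effect also assumes a paired t-test. The error touches the ADL-decline calculation alone. The loss is modest, but the study's only enrolment target is wrong as written and has to be corrected.

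**What to change.** Correct the closing sentence of the sample-size paragraph in one of two ways.

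1. **Raise the target.** State that 204 evaluable patients at 30% dropout need 204 / 0.70 = 292 enrolled. This costs 27 more patients.
2. **Keep 265 and restate what it delivers.** Say that it yields about 185 evaluable patients at 30% dropout, that 204 remain only if dropout is at most 23%, and what effect is detectable at n = 185 with the power and test used for the 204. This costs one sentence and a slightly less favourable figure, with no extra patients.

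Trial status reports that data collection is already under way, so the second option is the easier one to adopt. In either case, the sentence should name 204 as the base and show the division by 0.70. It should also say that 250 and 171 remain covered by 265.

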### Variables and data collection

Data will be collected from patients at baseline during their hospital stay, and at two follow-up time points (3 and 6 months post-discharge, see Fig. 1 for an overview of the study procedure). Patients’ medical records as well as routine clinical assessments and additional questionnaires will be used to collect information on self-management and its related factors as well as geriatric syndromes.

During baseline data collection, each patient will undergo an encompassing geriatric assessment performed by medical staff on the wards. This includes the following assessments:

Geriatric Screening for *functioning* as proposed by Lachs [39].Level of *independence* in ADLs and instrumental ADLs (iADLs) as assessed by the Barthel Index [35] and Blaylock Score [40]. The Blaylock Score assesses independent management of finances, medication, use of transportation, grocery shopping, and meal preparation.Level of *Loneliness* as assessed by the UCLA 3-Item Loneliness Scale [41].*Cognition* (normal, mild or moderate/severe cognitive problems) as assessed by the Montreal Cognitive Assessment (MoCA) [42] or Mini Mental Status Examination (MMSE) [43].*Mobility* as measured by the Timed Up and Go (TuG) [44] and Tinetti-Test [45].*Depressive symptoms* according to the Geriatric Depression Scale (GDS) [46].*Hand grip strength* in kg as a marker for physical strength.

In addition, the following sociodemographic and health-related parameters will be taken from the patients’ medical records:

*Age, sex, highest education level, marital state* and living situation/*housing*.Use of *aids*, *care* level, *help at home*, *healthcare utilization* (e.g. number of doctor or physician consultations or regular therapy).*Diagnoses* and number of *medications*.

These assessments and parameters will serve as independent variables related to self-management. For the assessment of self-management itself and further related factors, the following self-report questionnaires were selected based on the previous literature cited above. The questionnaires will be filled out with the assistance of trained study staff:

*Self-management* assessed by the Patient Activation Measure (PAM) [47, 48] and Appraisal of Self-Care Agency Scale-Revised (ASAS-R) [49, 50], with the former primarily assessing *confidence* in self-management abilities, and the latter evaluating self-management *behaviour*.*Self-Efficacy* as assessed by the generalised self-efficacy scale [51].*Anxiety* measured with five items from Becks Anxiety Index (BAI) [52] according to the scale used in the Survey of Health, Aging, and Retirement in Europe (SHARE) [53].Quality of Life (*QoL*) as assessed by the short form of the WHO-Quality of Life Questionnaire (WHOQOL-Bref) [54]. This questionnaire also covers satisfaction with social network, mental and physical health, and living environment.Health Locus of Control (*HLC*) as assessed by the German Fragebogen zur Erhebung von Kontrollüberzeugungen zu Krankheit und Gesundheit (KKG) [55, 56].Views on aging (*VoA*) and subjective age as assessed by the questionnaire used in the German Ageing Survey (Deutscher Alterssurvey, DEAS) [57, 58].

To determine the occurrence and significance of geriatric syndromes, the next step is to utilise a self-created questionnaire using Visual Analogous Scales (VAS). Patients will be requested to select the geriatric syndrome that they are experiencing from a list of options (multiple choice), and to indicate the syndrome that has the greatest impact on their lives (single choice):

Impaired mobility (walking, stairs).Gait problems, falls.Cognitive decline/memory problems.Depressive symptomology.Loneliness.Pain.Incontinence.Sleeping problems.Dysphagia.

Patients are then asked to indicate on a scale of 0 to 100,

how much the respective syndrome affects their daily life,whether they would attribute the syndrome to an illness (0) or old age (100),how worried they are that the respective syndrome will worsen,and how confident they are that the syndrome will improve.

